### Intervention and comparator descriptions

Patients will be followed with weekly visits during the up-titration phase. For nebivolol, the initial dose will be 1.25 mg once daily. If tolerated, it will be increased to 2.5 mg once daily by the end of week 1, 5 mg once daily by week 2 (visit 1), and 10 mg once daily by week 4 (visit 2). For carvedilol, the initial dose will be half of a 3.125-mg tablet twice daily. If tolerated, it will be increased to 6.25 mg twice daily by the end of week 1, 12.5 mg twice daily by week 2 (visit 1), and 25 mg twice daily by week 4 (visit 2). If side effects attributable to the study medications occur, up-titration will be delayed, the dose will be decreased, or the administration of the drug will be temporarily discontinued. If up-titration is not clinically feasible, either because of hypotension or bradycardia, the previous dose will be administered subsequently as the maximal tolerable dose. This process is illustrated in Fig. 2.

**Fig. 2 Fig2:**
[figure not shown]
Titration scheme of the study drug

### Follow-up protocol

On achievement of the target dose or the maximum tolerable dose, patients will be followed up clinically every month for the first 3 months, then every 3 months until the end of the study at 12 months. At each visit, patients will undergo a complete physical examination, medical history-taking, and assessment of drug compliance. Investigators will evaluate all clinical and laboratory adverse events at each visit. NYHA functional class and predefined clinical events will be recorded at each clinical visit. Echocardiographic examinations will be performed at 6 and 12 months after discharge.

### Adverse effects

Analysis of safety-related data will be performed with respect to frequency of serious adverse events (SAE), stratified by causality and intensity of morbidity in both treatment groups. Patients will be interviewed at each visit about the occurrence of any adverse events, including the time of onset, duration, and severity; all information will be recorded on a Case Report Form. The causal relation to the study drug and the intensity of adverse events will be evaluated by the investigators. SAE must be reported to the Institutional Review Board and study sponsor by the principal investigator within 24 h after the SAE becomes known.

### Withdrawals

Patients are free to withdraw from participation in the trial at their own request at any time and without giving reasons for their decision. Moreover, the primary investigator can withdraw study patients if continuation of the trial would be detrimental to the patient’s wellbeing. Withdrawals will be documented in the Case Report Form and in the patient’s medical records and all ongoing SAE will be followed up.

### Sample size

Calculation of sample size was done based on the primary outcomes and the primary analysis for the intention-to-treat population. The sample size was calculated using the study’s primary objective, to detect a difference in E/E’ of 5.0 between nebivolol and carvedilol treatment with a power of 90 %. On the basis of previous reports, we assume the standard deviation of E/E’ to be approximately 5.0 in both treatment groups [11, 12]. We adjusted the sample size for an estimated follow-up loss rate of 30 %, a two-sided level of significance *a* = 5 % and a power of 1 − β = 90 %. Thirty-one patients in each group are required to detect statistical differences with a two-sided Student’s *t* test given these parameters. Therefore, a total of 62 patients will be included in the analysis. The statistical analyses will be performed on the full dataset, which will include data from all randomized patients receiving at least one dose of study medication. Patients who are judged to be ineligible after study registration will be excluded from the analysis. Given the sample size, this study is likely to be underpowered in terms of assessing secondary outcomes.

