### Study design

This study is a prospective, randomized, open-label, single-centre, active controlled study with two parallel study groups. The choice of a prospective and open-label study was felt to be a reasonable reflection of clinical practice in only one center with a small sample. The randomized design was adopted to minimize bias in this single-center study. The dose of nebivolol was chosen on the basis of the SENIORS study [6]. The control arm will receive carvedilol because it is the β-Blocker that is indicated for the broadest population and is the most frequently used β-Blocker worldwide. A treatment duration of a minimum of 12 months was selected as a result of the SENIORS trial. The overall study design is depicted in Fig. 1.

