### Outcome measurements

The primary efficacy variables are mitral inflow velocities (E and A waves), deceleration time of the E wave (DT), isovolumetric relaxation time (IVRT), mitral annular velocities (early diastolic velocity of mitral annulus (Ea) and late diastolic velocity of mitral annulus (Aa) waves), left atrial (LA) volume, and LA strain (global systolic and diastolic LA strain), which will be measured via echocardiographic evaluation after 12 months of treatment. Mitral E/A and E/Ea ratios will be calculated. Parameters from Doppler analysis, M-mode echocardiography, and 2D-transthoracic echocardiography will be used. All echocardiographic images will be interpreted by an observer who is blinded to clinical data.

Secondary outcomes include occurrence of clinical events. Symptom severity (NYHA classification) and hospitalization will be evaluated at baseline and at maintenance follow-up visits. Vital signs, including heart rate and blood pressure, will be measured at every visit. Any complications, discontinuations, and deaths occurring during the study period will be noted. Each patient’s medical history and the results of a clinical examination will be recorded at baseline by the attending physician.

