### Statistical analyses

The intent-to-treat (ITT) analysis set will be used for efficacy analyses. All patients who have begun treatment will be included irrespective of their protocol adherence and continued participation in the study. Patients will be analyzed according to their randomized study medication irrespective of whether a SAE occurred before or following discontinuation of study medication. For baseline characteristics, continuous variables will be assessed using the Student’s *t* test and discrete variables will be compared using the chi-square test. The primary outcome will be compared using two-sample *t* tests. The two-sided null hypothesis for the primary outcome measure states that nebivolol and carvedilol lead to the same change in ventricular diastolic function during the 12 months after diagnosis. This null hypothesis will be tested by regression analysis adjusted for baseline values. Assessments for other echocardiographic indices will be compared between treatment groups after 12 months of follow-up using two-sample *t* tests. Analyses of changes will be performed using data from all patients for whom baseline and 12-month follow-up data are available. Event-free cumulative survival rates will be plotted using the Kaplan-Meier method and comparisons will be made between patients given nebivolol and carvedilol using the log-rank test. A Cox proportional hazards model, with the use of forward selection based on the likelihood ratio test, will be implemented for multivariate analysis to determine which prognostic factors identified in the univariate analysis, including mitral inflow velocities, DT, IVRT, mitral annular velocities, LA volume, and LA strain were significantly related to clinical events in the follow-up period.

A safety analysis dataset will be used to assess safety and tolerability variables. All patients who received at least one dose of nebivolol or carvedilol, and for whom post-dose data are available, will be included in the safety population. Patients will be censored 7 days after their last dose of study medication. A value of *p* < 0.05 will be considered statistically significant.

Potential attrition bias will be mitigated by conducting dropout analysis and intention-to-treat analysis. Given that dropouts are expected, multiple imputation, based on regression methods, will be performed to complete the data. A fully specified statistical analysis plan will be written before unmasking of the data.

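### Randomised, treated patients later judged ineligible are excluded by one section and included by another, and in this open-label trial nothing ties that judgement to pre-randomisation data or a blinded assessor

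*Protocol article*

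**What the plan says.** Two sections of the protocol article define who enters the efficacy analysis.

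- **Sample size.** It opens by naming the population: "Calculation of sample size was done based on the primary outcomes and the primary analysis for the intention-to-treat population". It then describes the dataset as "data from all randomized patients receiving at least one dose of study medication", and adds: "Patients who are judged to be ineligible after study registration will be excluded from the analysis".
- **Statistical analyses.** "The intent-to-treat (ITT) analysis set will be used for efficacy analyses". The definition follows: "All patients who have begun treatment will be included irrespective of their protocol adherence and continued participation in the study". This section has no exclusion for ineligibility.

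Three other places bear on the point.

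- **Study design:** "This study is a prospective, randomized, open-label, single-centre, active controlled study with two parallel study groups".
- **Outcome measurements:** "All echocardiographic images will be interpreted by an observer who is blinded to clinical data".
- **Table 1:** most criteria are factual, but two are matters of judgement. One is the investigator's opinion that a condition makes participation unsafe or unsuitable; the other is concern about the patient's ability to comply with procedures or follow-up.

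The article does not say who judges late ineligibility, when, on what data, or with what knowledge of arm and outcome.

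**The concern.** Randomisation makes the arms comparable only if everyone randomised, or a subset chosen without reference to arm or later course, is analysed. A rule that removes patients after randomisation on a judgement is safe if the judgement uses only facts fixed before randomisation and is made by someone who knows neither arm nor outcome. The stated rule carries neither condition, and the treating side knows the arm. With 31 patients per arm, a few selective removals could move the primary comparison.

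The article also relies on intention-to-treat analysis as a protection. The Statistical analyses section offers it against attrition bias, and the Discussion rates the risk of selection bias as low. An open exclusion rule weakens both statements.

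**Working it through.** **1. The two sections compared, by type of patient**

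| Randomised patient | Sample size section | Statistical analyses section |
|---|---|---|
| Never dosed | out | out |
| Dosed, poor adherence or early stop | in | in |
| Dosed, later judged ineligible | **out** | **in** |

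The sections differ only in the third row.

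**2. Does the exclusion act after randomisation?** Registration is not defined. Under Randomization, only patients who meet all eligibility requirements are randomised. The exclusion sentence directly follows a description of the dataset as randomised, dosed patients. If it concerned only people removed before randomisation, it would take nobody out of that dataset. Exclusion after randomisation is therefore the natural reading, though not the only possible one.

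**3. The plan's own sample size.** Inputs from the Sample size section: difference 5.0, SD 5.0, two-sided alpha 5%, power 90%, follow-up loss 30%.

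- n per arm = 2 × (1.95996 + 1.28155)² × 5.0² / 5.0² = 21.01
- Allowing for loss: 21.01 / (1 − 0.30) = 30.02, rounded up to **31**, or 62 in total. The stated figure reproduces.

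The 30% covers follow-up loss only. By the exact t test, power is 97.2% with 31 per arm observed and 90.0% with 22 per arm, about what remains after the planned loss. One further exclusion per arm (21) gives 88.5%, and two (20) give 86.9%. The cost in power is small; bias is the main issue.

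**4. How large could the bias be?** The documents give no number of exclusions, so this part rests on an assumption. Simulate 40,000 trials with no true difference and SD 5, remove the m highest (worst) E/E' values from one arm only, and apply an unadjusted two-sample t test at two-sided 5%. For 22 per arm, the removals come out of the 22.

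| Removed from one arm | 31 per arm: type I error | 31 per arm: shift in difference | 22 per arm: type I error | 22 per arm: shift in difference |
|---|---|---|---|---|
| 0 | 4.9% | about 0 | 4.9% | about 0 |
| 1 | 6.4% | 0.34 | 6.7% | 0.46 |
| 2 | 8.9% | 0.64 | 9.3% | 0.84 |
| 3 | 12.5% | 0.91 | 14.1% | 1.20 |

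The shift favours the arm that loses its worst values. With 31 per arm and three removals it is 0.91 / 5.0 = 18% of the planned difference; with one removal it is 0.34 / 5.0 = 7%.

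**The case against.** **Adherence and eligibility differ.** Adherence describes conduct after entry and eligibility describes status at entry, so the exclusion can be read as a specific exception to a general rule. This stands in part. It would be too strong to say that the two sections cannot both be followed. They must still be reconciled, because the set is called intention-to-treat and the section that defines it mentions no such exception.

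**The never dosed.** A reader might infer that the sections also contradict each other on patients who took no dose. They do not: both require treatment to have started. That is a common modified intention-to-treat rule under a looser label.

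**The mechanism is inferred.** A reader might conclude that almost any patient who does badly could be removed, or that an unblinded review is planned. The text supports neither. Table 1 lists entry criteria, none of them an E/E' or other diastolic value, and late findings of ineligibility should be uncommon if screening works as described. What stands is narrower: the rule is open, some criteria rest on opinion, and treatment is known.

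**Safeguards exist or will come.** The blinded echocardiogram reader protects the measurement, not the choice of who is analysed. A full analysis plan is promised before the data are unmasked and may well set timing and adjudication. The exclusion itself, however, is already fixed in the article and conflicts with the definition beside it, so it is not a detail merely left for later.

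**The figures are extreme.** This stands. They assume that exactly the highest values are removed, always from the same arm, and they use an unadjusted t test although the article also specifies a regression adjusted for baseline.

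**Conclusion.** The point holds for one group: randomised, treated patients later judged ineligible. The article excludes them in one section and includes them in the other. As worded, the rule permits exclusion after randomisation that could depend on arm or outcome.

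The article does not show that such exclusion is intended or likely. The figures with 31 per arm (type I error about 6% to 13%, shift about 0.3 to 0.9 for one to three removals) mark an extreme case for removals from a single arm. They are not an expected bias. If exclusions are unrelated to arm and outcome, this bias does not arise. The conclusion rests on reading the exclusion as acting after randomisation, which the order of the text favours.

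The matter should be fixed because it decides who enters the primary comparison and the remedy is cheap. It does not invalidate the design.

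**What to change.** 1. Delete the exclusion sentence from the Sample size section. State that randomised, treated patients stay in their assigned arm in the primary efficacy set whatever later eligibility findings show.
2. If an eligibility exclusion is wanted, use it only as a sensitivity analysis, based on data recorded before randomisation and judged by someone blind to arm and outcome.
3. For never-dosed patients, choose one course. Either call the set modified intention-to-treat, or change both the one-dose condition in the Sample size section and the started-treatment condition in the Statistical analyses section to all randomised patients. Changing only one would create a new conflict.

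The cost is wording only, and the sample size stays at 62. The downside is that a few ineligible patients may slightly dilute the estimated difference; the sensitivity analysis would show whether that matters.

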### Data collection, storage, and security

All paper files are to be stored in locked file cabinets, and electronic files are to be stored in password-protected, encrypted files. Both paper and electronic files will be accessed only by members of the research team. The final dataset will reside with the principal investigator.

### Statistical analyses

The intent-to-treat (ITT) analysis set will be used for efficacy analyses. All patients who have begun treatment will be included irrespective of their protocol adherence and continued participation in the study. Patients will be analyzed according to their randomized study medication irrespective of whether a SAE occurred before or following discontinuation of study medication. For baseline characteristics, continuous variables will be assessed using the Student’s *t* test and discrete variables will be compared using the chi-square test. The primary outcome will be compared using two-sample *t* tests. The two-sided null hypothesis for the primary outcome measure states that nebivolol and carvedilol lead to the same change in ventricular diastolic function during the 12 months after diagnosis. This null hypothesis will be tested by regression analysis adjusted for baseline values. Assessments for other echocardiographic indices will be compared between treatment groups after 12 months of follow-up using two-sample *t* tests. Analyses of changes will be performed using data from all patients for whom baseline and 12-month follow-up data are available. Event-free cumulative survival rates will be plotted using the Kaplan-Meier method and comparisons will be made between patients given nebivolol and carvedilol using the log-rank test. A Cox proportional hazards model, with the use of forward selection based on the likelihood ratio test, will be implemented for multivariate analysis to determine which prognostic factors identified in the univariate analysis, including mitral inflow velocities, DT, IVRT, mitral annular velocities, LA volume, and LA strain were significantly related to clinical events in the follow-up period.

A safety analysis dataset will be used to assess safety and tolerability variables. All patients who received at least one dose of nebivolol or carvedilol, and for whom post-dose data are available, will be included in the safety population. Patients will be censored 7 days after their last dose of study medication. A value of *p* < 0.05 will be considered statistically significant.

Potential attrition bias will be mitigated by conducting dropout analysis and intention-to-treat analysis. Given that dropouts are expected, multiple imputation, based on regression methods, will be performed to complete the data. A fully specified statistical analysis plan will be written before unmasking of the data.

The report presenting the primary findings from this study will follow the Consolidated Standards of Reporting Trials (CONSORT) 2010 guidelines. Study results will be disseminated to researchers and clinicians via publications and conference presentations. Authorship of published papers will follow established guidelines for defining the level of contribution that warrants authorship.

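### The protocol attaches both a two-sample t test and a baseline-adjusted regression to the primary outcome and does not say which one decides

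*Protocol article*

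**What the plan says.** The Statistical analyses section makes three statements on this point.

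- Primary outcome: "The primary outcome will be compared using two-sample" t tests.
- Primary hypothesis: "The two-sided null hypothesis for the primary outcome measure states that nebivolol and carvedilol lead to the same change in ventricular diastolic function" over the 12 months after diagnosis, followed by "This null hypothesis will be tested by regression analysis adjusted for baseline values".
- Remaining indices: "Assessments for other echocardiographic indices will be compared between treatment groups after 12 months of follow-up using two-sample" t tests.

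The Sample size section says that its calculation rests on the primary analysis. The target is "to detect a difference in E/E’ of 5.0 between nebivolol and carvedilol treatment", with the standard deviation assumed "to be approximately 5.0 in both treatment groups", 90 % power, two-sided 5 % significance and 30 % loss to follow-up. It concludes: "Thirty-one patients in each group are required to detect statistical differences with a two-sided" Student's t test.

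Both methods come under the same threshold of p < 0.05. Neither is labelled primary, supportive or sensitivity. The Abstract and the Randomization section show that echocardiography is done before randomization, so a baseline value should exist for each patient.

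**The concern.** One hypothesis has two named analyses, and they can return different p-values from the same data. The t-test sentence cannot be read as covering only the remaining echocardiographic indices, because those have their own sentence.

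The t-test sentence also leaves its variable open. The null concerns change, so the test could be on change from baseline. The sentence for the other indices speaks of comparison after 12 months, so it could equally be on 12-month values. These two t tests behave differently.

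At stake is the reading of a small trial. With about 22 evaluable patients per arm, whether the result counts as significant can depend on which analysis is reported. A team free to choose after seeing both results would have a false-positive rate above 5 %.

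**Working it through.** **Inputs from the protocol.** Difference 5.0, SD 5.0, two-sided 5 % significance, 90 % power, 30 % loss, 31 per group, 1:1 allocation.

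**Assumption.** The correlation ρ between baseline and 12-month E/E' is not in the protocol, so a range of 0.3, 0.5 and 0.7 is shown. The SD of 5.0 is taken to apply to E/E' at both time points.

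**1. Reproduce the plan's figure.** n per arm = 2(z₀.₉₇₅ + z₀.₉₀)² × SD²/difference² = 2 × (1.960 + 1.282)² × 25/25 = 21.01. Allowing for loss: 21.01/0.7 = 30.02, rounded up to 31. This matches. Rounding before inflating gives 22/0.7, so 32. The exact t calculation gives 22.02, so 32 or 33 depending on rounding. All lie within two patients of the stated figure. The stated size is therefore that of an unadjusted t test with no baseline correlation. Expected completers: 31 × 0.7 = 21.7, about 22 per arm.

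**2. Spread that each analysis works with.**

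- 12-month t test: SD 5.0.
- Baseline-adjusted regression: residual SD = 5√(1 − ρ²) = 4.77, 4.33, 3.57.
- Change-score t test: SD = 5√(2(1 − ρ)) = 5.92, 5.00, 3.87.

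Relative to the 12-month t test, adjustment removes a share ρ² of the variance (9 %, 25 %, 49 %) and costs one degree of freedom.

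**3. Power at 5.0 points** (noncentral t, 21.7 per arm). The 12-month t test has 89.6 %. The regression has 92.1 %, 96.0 % and 99.4 % at ρ = 0.3, 0.5 and 0.7. In simulation with 22 per arm, the change-score t test has 78 %, 90 % and 99 %.

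**4. How often the verdicts differ.** Simulation of 40,000 trials per setting, 22 completers per arm, each test at two-sided 0.05. A repeat with a different random seed agreed to within a few tenths of a percentage point.

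| Quantity | ρ = 0.3 | ρ = 0.5 | ρ = 0.7 |
|---|---|---|---|
| No true difference: 12-month t test or regression significant | 6.4 % | 7.6 % | 8.3 % |
| No true difference: change-score t test or regression significant | 7.9 % | 7.5 % | 6.9 % |
| True difference 5.0: 12-month t test and regression disagree | 4.4 % | 7.3 % | 9.8 % |
| True difference 5.0: change-score t test and regression disagree | 16.0 % | 7.5 % | 1.0 % |
| True difference 2.5: 12-month t test and regression disagree | 9.3 % | 18.0 % | 31.9 % |
| True difference 2.5: change-score t test and regression disagree | 20.4 % | 17.9 % | 13.8 % |

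Disagreement here means that one test is significant and the other is not. It does not mean significant effects in opposite directions.

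**The case against.** The strongest reply is that the protocol does give an order. Only the regression is expressly tied to the formal null; the t-test sentence speaks merely of a comparison. On that reading the preferred analysis is already in place and the t test is a plain description. Much of this stands: it would be wrong to say that nothing in the text favours either test. It does not settle the matter, because the Sample size section refers to the primary analysis and then uses a Student's t test.

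A second reply is that a fully specified analysis plan is promised before unmasking and that this is a condensed article. An analysis plan can indeed settle the choice, which lowers the urgency. But these are two statements that pull apart, not a missing detail, so the analysis plan would have to demote one of them. The deadline also protects less than usual: the treatment is open-label, and the only blinding described is that of the echocardiogram reader.

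Stronger readings are tempting, and the protocol does not support them:

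- *The type I error is inflated as planned.* The protocol states no rule that a win on either test suffices. The 6.4 to 8.3 % applies only if such a rule were used.
- *Power is being lost.* That follows only if the t test is made decisive, and on 12-month values it still gives about the 90 % that was planned.
- *The sample size is wrong.* It reproduces, and sizing on a t test while analysing with adjustment is conservative.
- *A chance baseline imbalance feeds straight into the t test.* This holds for a test on 12-month values, but not in that form for a test on change.
- *The unadjusted tests of the other indices are an error.* They are valid under randomization, only less efficient.

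**Conclusion.** The ambiguity is real and does not depend on any assumed figure: the formal null points to the regression, the sample size points to the t test, and the variable for the t test is not stated. It should be fixed, but it does not invalidate the design.

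Its size depends on the unknown correlation. Over 0.3 to 0.7 the possible excess type I error is moderate: about 1.4 to 3.3 percentage points above 5 % if either the 12-month t test or the regression could count. At the planned effect those two verdicts split in up to about one trial in ten, and at half that effect in up to about one in three. If the t test is on change, the pattern reverses: at the planned effect disagreement is largest at low correlation (16 %) and almost vanishes at 0.7 (1 %).

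Across the range the regression is the more powerful of the analyses considered. The advantage over the 12-month t test is small at 0.3 (about 2.5 points) and large at 0.7 (about 10 points). These figures assume normal data with equal SDs of 5.0 at both visits and complete data on 22 patients per arm.

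**What to change.** State in the protocol, and carry into the analysis plan, that the single primary test is the treatment coefficient, with its 95 % CI, from a linear model of 12-month E/E' on arm and baseline E/E'. Delete the sentence on t tests for the primary outcome, or label that comparison descriptive and say whether it uses 12-month values or change. Keep 31 per group, and add a line saying that the t-test calculation is conservative for the adjusted analysis.

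Optionally, as a gain in efficiency and not the correction of an error, use the same baseline-adjusted model for the other echocardiographic indices.

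The cost is a change of wording and one degree of freedom per model. No extra patients, visits or measurements are needed. The change should be dated before any outcome comparison by arm is seen.

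### The primary outcome is given both an unadjusted t test and a baseline-adjusted regression, with no statement of which one decides

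*Protocol article*

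**What the plan says.** All references are to the protocol article.

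- Statistical analyses, first statement: "The primary outcome will be compared using two-sample" t tests.
- Statistical analyses, next sentence: the primary null hypothesis "states that nebivolol and carvedilol lead to the same change in ventricular diastolic function during the 12 months after diagnosis".
- Statistical analyses, the sentence after that: "This null hypothesis will be tested by regression analysis adjusted for baseline values". Two-sample t tests are then assigned to the remaining echocardiographic indices.
- Statistical analyses, one threshold for everything: a p value below "0.05 will be considered statistically significant".
- Outcome measurements: the primary variables are those "which will be measured via echocardiographic evaluation after 12 months of treatment".
- Sample size: the calculation is said to rest on the primary analysis. It takes a difference in E/E' of 5.0 and an SD of E/E' of about 5.0, and concludes that 31 patients per group "are required to detect statistical differences with a two-sided Student’s" t test.

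**The concern.** An unadjusted t test and a regression on baseline are separate procedures, and on the same data they can fall on opposite sides of 0.05. The article calls neither of them primary, supportive or sensitivity. The cues also conflict: the null hypothesis is attached to the regression, but the sample size and its reference to the primary analysis are attached to the t test. Whichever result is reported as the main one, a sentence in the protocol can be cited for it.

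At stake is the error rate of the trial's main comparison, and whether a moderate effect is declared significant because of a choice that the protocol leaves open. The treatment is open-label. Blinding is described only for the echocardiographic reading, so the order of the tests is best fixed in the protocol text.

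**Working it through.** **Inputs.** From the Sample size section: difference 5.0, SD 5.0, two-sided 5 %, power 90 %, loss 30 %, 31 per group. The baseline to 12-month correlation r of E/E' is not given. It is assumed to lie between 0.3 and 0.7, with r = 0 as a limiting case.

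**1. The plan's own figure.** n per group = 2 × (1.960 + 1.282)² × (5.0/5.0)² = 21.01. Allowing for 30 % loss, 21.01/0.70 = 30.02, which rounds up to 31. The stated 31 is reproduced. Evaluable patients: 31 × 0.70 = 21.7, taken as 22 per arm. The noncentral-t power of a t test on 12-month values at 22 per arm is 90.0 %.

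**2. How closely the two tests agree under the null.** With equal variances at both times, the correlation between the unadjusted and the adjusted treatment estimate is √(1 − r²): 0.95, 0.87 and 0.71 at r = 0.3, 0.5 and 0.7. They are strongly correlated but not the same test.

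**3. Error and disagreement.** Simulated bivariate-normal trials, 22 per arm. Ranges show the spread between independent simulation runs.

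| | r = 0.3 | r = 0.5 | r = 0.7 |
|---|---|---|---|
| Either test alone, null true | 5.0 % | 5.1 % | 5.0 % |
| Either p < 0.05 counts, null true | 6.4–6.6 % | 7.3–7.4 % | 8.0–8.3 % |
| Tests disagree, true difference 2.5 | about 10 % | 18 % | 32 % |
| Tests disagree, true difference 5.0 | 4–4.5 % | 7 % | 10 % |

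**4. Power for a difference of 5.0, 22 per arm.** Noncentral t. The residual SD for the regression is 5√(1 − r²). The SD of change is 5√(2(1 − r)).

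| | r = 0 | r = 0.3 | r = 0.5 | r = 0.7 |
|---|---|---|---|---|
| t test on 12-month values | 90.0 % | 90.0 % | 90.0 % | 90.0 % |
| Regression: residual SD | 5.00 | 4.77 | 4.33 | 3.57 |
| Regression: power | 89.9 % | 92.4 % | 96.2 % | 99.5 % |
| t test on change: SD | 7.07 | 5.92 | 5.00 | 3.87 |
| t test on change: power | 63.0 % | 78.2 % | 90.0 % | 98.7 % |

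Simulated power for the regression is slightly lower than these values (89.2 % at r = 0, 91.7 % at r = 0.3), because the formula ignores chance imbalance in baseline.

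**5. Twelve-month value or change.** Write the regression as Y = a + τT + βX + e, where Y is the 12-month value, T the treatment and X the baseline. Subtracting X from both sides gives Y − X = a + τT + (β − 1)X + e. The treatment effect τ, its standard error and its p value are unchanged. Under the regression, a null stated on change and an outcome stated at 12 months are therefore the same test. Under a t test they are not.

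**The case against.** The best defence is that the section states one null hypothesis for the primary outcome and gives it one test, the regression. It then reserves t tests for the other indices. On that reading the earlier t-test sentence is only descriptive, and nowhere does the article say that either p value suffices. A full analysis plan is also promised before unmasking, and labelling a supportive analysis is ordinary content for it. This is probably what was intended, and it lowers the stakes. It does not remove the contradiction: the t-test sentence names the primary outcome without qualification, and the Sample size section links the primary analysis to a t test. A later analysis plan would have to override one of the two published statements.

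A reader might also infer that the 90 % power depends on which of the two tests is used, or that the trial is undersized. The documents do not support this. The t test on 12-month values has 90 % power, and the regression has practically that or more. The shortfall in step 4 needs a third procedure, a t test on change scores with r below 0.5. The section does mention analyses of change, but never explicitly assigns such a t test to the primary outcome.

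Nor is the mismatch between a 12-month outcome and a null on change a separate fault if the regression is used (step 5).

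**Conclusion.** The point holds as a contradiction about the primary test and should be fixed, but it does not undermine the design. Two tests are assigned to the primary outcome at the same threshold without a ranking, and the document's own cues point in both directions.

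The inflation to about 6.4 to 8.3 % is conditional. It assumes that whichever test succeeds is allowed to count, that 22 patients per arm are evaluable, that the data are roughly normal with equal variances, and that r lies between 0.3 and 0.7. Disagreement between the tests is largest for moderate effects, at about 10 to 32 % for a difference of 2.5. It is smaller, about 4 to 10 %, at the difference the trial was designed to detect.

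The stated sample size and power stand. Ninety per cent is exact for the t test on 12-month E/E' and essentially a floor for the regression (about 89 to 90 % at r = 0, higher otherwise).

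All error figures are for one variable. The Outcome measurements section lists several primary variables. That multiplicity is a separate matter, and a single named test holds 5 % only if E/E' is also the sole primary variable.

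**What to change.** In Statistical analyses, name one primary test: linear regression of 12-month E/E' on treatment with baseline E/E' as covariate, two-sided 5 %. E/E' is the variable used for the sample size, and the regression is the test already attached to the null hypothesis. Delete the sentence that assigns t tests to the primary outcome, or label that t test supportive and without a claim.

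In Sample size, add that the 90 % power was computed for an unadjusted t test on 12-month E/E' and is approximately a lower bound for the regression.

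The cost is wording in the protocol, with matching text in the analysis plan. The baseline echocardiogram is already collected, and no visit, measurement or patient number changes.
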